The main goal of study 2 is to determine whether visuospatial perspective-taking or conventional verbal training is more effective in enhancing children’s mind and emotion understandings. ToM training has mostly been heavily language-based because the literature has identified language as a strong correlate of ToM development [42, 44]. Visible social interaction without language input does not promote false-belief understanding. Hence verbal interaction is regarded to be crucial to mind understanding [88]. Moreover, a study by Lohmann and Tomasello [44] involving 3-year-old children also found that training on the theory of mind with minimal linguistic interaction was ineffective in improving children’s false belief understanding. On the basis of the embodiment framework, study 2 will investigate whether simulating the visuospatial experiences of others alone, i.e. *without* the presence of verbal communication, is sufficient to enhance mind and emotion understanding. By doing this, study 2 will compare the training effect caused by visuospatial perspective-taking to the one caused by mere verbal interaction. In study 2, children aged 4.5 years will be randomly assigned to participate in either (a) *socialised altercentric block building* (both visuospatial perspective-taking and verbal interaction), (b) *parallel altercentric block building* (visuospatial perspective-taking only), or (c) *paired dialogic reading* (verbal interaction only). Dialogic reading will be served as a promising interactive approach because this training involves back-and-forth verbal exchanges between children. In addition, dialogic reading is easy to administer with preschool children. The differences between groups in ToM and emotion understanding post-training would indicate whether visuospatial perspective-taking or verbal interaction group will be more effective in fostering mental state understandings. Two research questions will be addressed in study 2:

(1) What is the difference between the effect of visuospatial perspective-taking vs. general verbal interaction training on improving preschoolers’ ToM and emotion understanding?

(2) Do children trained in the socialised altercentric block building group improve significantly more than children in the parallel altercentric block building and paired dialogic reading groups in ToM and emotion understanding after 6 weeks of training?

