#### Data analysis plan

The preliminary analyses will be the same as those in study 1. Next, repeated measures MANOVAs will be conducted to compare the effectiveness of the three trainings in improving children’s visuospatial perspective-taking, ToM, and emotion understanding abilities. We predict all of the training in study 2 will increase children’s ToM and emotion understanding. In particular, we hypothesise that the *socialised altercentric block building* training will result in the greatest improvement on the children’s ToM and emotion understanding. We expect the paired dialogic reading to enhance children’s general language ability but not their visuospatial perspective-taking ability. In contrast, we expect that the *parallel altercentric block building* will enhance the children’s visuospatial perspective-taking ability but not their general language ability. We further hypothesise that the *socialised altercentric block-building* training will enhance both visuospatial perspective-taking and language abilities because verbal interaction may strengthen children’s developing ability to simulate the visuospatial experience of others. This finding will reveal whether visuospatial perspective-taking is conducive to developing ToM beyond the contribution of verbal interaction.

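### Study 2 ties its conclusion about ToM beyond verbal interaction to a training check, and the wider reading of that sentence is not the right contrast either

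*Protocol article*

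**What the plan says.** The Study 2 Data analysis plan proceeds in this order.

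- Analysis: "repeated measures MANOVAs will be conducted to compare the effectiveness of the three trainings in improving children’s visuospatial perspective-taking, ToM, and emotion understanding abilities".
- ToM hypothesis: the socialised arm's "training will result in the greatest improvement on the children’s ToM and emotion understanding".
- Trained-skill hypotheses: reading should raise language but not perspective-taking, and parallel building the reverse. For the socialised arm, the "training will enhance both visuospatial perspective-taking and language abilities because verbal interaction may strengthen children’s developing ability to simulate the visuospatial experience of others".
- The next and last sentence: "This finding will reveal whether visuospatial perspective-taking is conducive to developing ToM beyond the contribution of verbal interaction".

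The section headed The present study gives a broader basis for inference: "The differences between groups in ToM and emotion understanding post-training would indicate whether visuospatial perspective-taking or verbal interaction group will be more effective". Its second research question for Study 2 asks whether socialised children "improve significantly more than children in the parallel altercentric block building and paired dialogic reading groups in ToM and emotion understanding".

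The table under Study 2, Training activities, marks the socialised arm as having both ingredients, the parallel arm as having perspective-taking only, and the reading arm as having verbal interaction only.

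**The concern.** Read as written, the closing sentence refers to the hypothesis directly before it. That hypothesis names two outcomes, perspective-taking and language, in one arm. Neither is ToM. A rise in the skills that were trained shows that the training took. It cannot show that ToM benefited, still less that it benefited beyond what verbal interaction gives.

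The sentence can be read more widely, to include the hypothesis that the socialised arm gains most in ToM. That does not settle the matter, because being best of three mixes two contrasts that answer different questions.

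At stake is the main theoretical claim of Study 2, whether perspective-taking contributes to ToM over and above language. Without a named contrast, a training check or a mixed criterion could be reported as the answer. A real contribution could also be missed.

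**Working it through.** **Step 1. What each contrast isolates** (table under Study 2, Training activities).

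| Contrast | Perspective-taking | Verbal interaction | What it isolates |
|---|---|---|---|
| Socialised − parallel | yes − yes | yes − no | verbal interaction added to perspective-taking |
| Socialised − reading | yes − no | yes − yes | perspective-taking added to verbal interaction |
| Parallel − reading | yes − no | no − yes | one ingredient against the other |

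The closing sentence asks the second question. Research question 2 bundles the first two. The hypothesis of greatest improvement is a ranking over all three arms. The plan ties the conclusion to none of the rows.

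**Step 2. The plan's own sample size.** Inputs from Study 2, Participants: f = 0.32, alpha 0.05, power 0.80, three groups, 98 children required, 40 per arm recruited, 20% attrition allowed. With two time points (pre-test and post-test), the group-by-time test has df1 = 3 − 1 = 2, df2 = N − 3 and noncentrality N × f². At N = 98 the noncentrality is 98 × 0.1024 = 10.04 and power is 0.804. N = 98 is the smallest N that reaches 0.80, so the stated figure reproduces and is not in dispute. After 20% attrition an arm of 40 has 32 children.

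**Step 3. Power of the contrast that answers the question.** Assume a pairwise d = 2 × 0.32 = 0.64 on the analysed scale; the plan gives no pairwise effect. For a two-sided 5% two-sample t-test, df = 2n − 2 and the noncentrality is d × √(n/2).

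- n = 32: 0.64 × √16 = 2.56, power 0.71.
- n = 40: 0.64 × √20 = 2.86, power 0.81.

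**Step 4. What the bundled criterion misses.** Suppose the true ToM gains in the socialised and parallel arms are equal and both exceed reading by 0.64. Perspective-taking then truly adds to verbal interaction.

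- Socialised − reading is significant in 71% (n = 32) to 81% (n = 40) of trials, as in Step 3.
- Socialised − parallel has a true difference of zero. It is significant in the socialised arm's favour in 2.5% of trials, the upper tail of a two-sided 5% test.
- Beating both arms can therefore occur in at most about 2.5% of trials.
- If the criterion is only to rank first, two truly equal arms split that place about evenly, so it is met about half the time, by chance.

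**Step 5. Joint analysis with perspective-taking.** The sentence naming the MANOVAs lists perspective-taking beside ToM and emotion understanding. It does not say whether they enter one multivariate test. Suppose they do. Assume a perspective-taking gain in both block arms at f = 0.32, and no ToM or emotion effect. With two equal arms against a third, d = 0.32 × 3/√2 = 0.68. Assume correlations of 0 to 0.5 between outcomes. Simulated change scores (4,000 trials per setting, Pillai's trace) give:

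| Outcomes in the test | 32 per arm | 40 per arm |
|---|---|---|
| Perspective-taking, ToM, emotion | 60–80% significant | 72–90% significant |
| ToM, emotion only | about 5% | about 5% |

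The first row is driven by perspective-taking alone.

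**The case against.** The strongest reply is that the closing sentence is a loosely worded summary, not a decision rule. The plan gives no threshold for it, and language is not among the outcomes listed for the MANOVAs. The real comparison is on ToM: The present study rests the inference on between-group ToM and emotion differences, and research question 2 names reading as a comparator. A socialised arm that beats both others necessarily beats reading.

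Much of this stands. A reader might infer that Study 2 ignores ToM, or that it would declare a ToM benefit whenever perspective-taking and language rise. The documents do not support that, because ToM is compared between arms in both sections. How often two trained-skill gains would both be significant under assumed gains is the power of a training check. It is not a false-conclusion rate for this plan and is not used here.

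Two things survive the reply. First, beating both arms is sufficient but not necessary, and Step 4 shows what that costs. Second, the general statement in The present study concerns which approach is more effective, not what one adds to the other.

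It may also be said that a condensed article leaves follow-up contrasts to a fuller plan. That would excuse silence. Here the article states an inference, and the finding it points to does not support it.

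**Conclusion.** The point holds in a limited form. The final sentence of the Study 2 analysis plan attaches a conclusion about ToM to a finding that, as worded, contains no ToM outcome. The wider reading brings ToM in but uses a criterion that mixes the effect of verbal interaction with that of perspective-taking. If the two block arms are equal and both better than reading, the criterion of beating both arms is met in at most about 2.5% of trials, against 71–81% for the contrast that answers the question.

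Those figures assume d = 0.64 on the analysed scale, 32 to 40 children per arm, two-sided 5% tests and no allowance for multiplicity. The MANOVA figures apply only if perspective-taking is analysed jointly with ToM, and they rest on the effect and correlations assumed in Step 5. The conclusion about logic depends on none of these numbers.

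Even the right contrast holds verbal interaction constant only nominally. Socialised children discuss the bear's viewpoint, whereas the reading arm keeps mental-state words to a minimum and has no block building.

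**What to change.** Replace the closing sentence with text to this effect:

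- Whether perspective-taking contributes to ToM beyond verbal interaction will be judged from the socialised minus paired dialogic reading contrast on ToMS, and separately on TEC. It will be analysed as pre-post change or as post-test adjusted for pre-test, and reported with a 95% CI.
- What verbal interaction adds to perspective-taking will be judged from the socialised minus parallel contrast.
- Gains in PTT-C and TOPOL-EV are training checks. They do not by themselves support a conclusion about ToM, and they stay out of the multivariate outcome set used for it.

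Unadjusted post-test scores should not be used, because the plan analyses change and the assumed d applies to that scale.

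The cost is a few sentences and one named contrast, with no new arms, measures or data. The downside is that the conclusion becomes harder to reach than through a training check or a joint MANOVA: pairwise power is about 0.71 with 32 per arm and 0.81 with 40, if d = 0.64 is assumed.

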## Discussion

This study proposes a novel visuospatial-based block-building training to complement the conventional ToM training. The findings are expected to have theoretical and practical implications. Theoretically, this research may advance our knowledge of the nature of mental state understanding in two ways: First, if our findings show that ToM and emotion understanding can be improved by training then this will give credence to the idea that individual variations in mental state understanding are not entirely the result of maturational or developmental cognitive processes, but are partially driven by social-environmental input. More notably, the proposed visuospatial-based training will be directly compared to the traditional language-based training, which addresses the contrasting theoretical accounts of social-cognitive development. To date, the dominant view has been that language and verbal interaction is the basis of ToM development. This study draws on the embodied cognition literature to explore the possibility that mind and emotion understanding may be influenced by our simulation of another person’s visuospatial experiences. The findings of this research may shed new light on how mind understandings develop and may further bridge the conceptually related but empirically isolated literature of ToM and visuospatial perspective-taking.

The study also has direct practical implications. There has been a wealth of evidence that early mental state understanding strongly predicts positive child outcomes, including social competence and academic performance [103–108]. As a result, researchers may collaborate with practitioners to develop evidence-based training to increase mind and emotion understanding. To date, ToM training has predominantly relied on verbal interaction. ToM training generally involves specific training in language (such as understanding sentential complements and mental state terms) or explicit conversation regarding mental states and the relationship to behaviour. Paradoxically, ToM interventions often target children with autism spectrum disorder (ASD), who commonly have oral language deficits. This place children with ASD under challenging circumstances. In that light, the present study proposes new avenues to train psychological perspective-taking, supposing the results will indicate that visuospatial perspective-taking in the form of block building is a feasible and effective training paradigm. In that case, this specific block-building training can be introduced to complement the conventional ToM training. Block play is popular among young children, especially children with ASD. The proposed block-building activities ought to be attractive to them. Moreover, as blocks are always accessible in kindergarten classrooms, this proposed block-building training may be implemented in regular early childhood education settings to improve young children’s ToM and emotion understanding.

## Data Availability

Not applicable.

## Abbreviations

ANOVA: The one-way analysis of variance
ASD: Autism spectrum disorder
fMRI: Functional magnetic resonance imaging
PTT-C: The perspective-taking test for children
RCPM: Raven’s Coloured Progressive Matrices
TEC: The Test of Emotion Comprehension
TEMA-3: The test of Early Mathematics Ability-3
ToMS: The Theory-of-Mind Scale
ToM: Theory of Mind
TOPOL-EV: The Hong Kong Test of Preschool Oral Language (Cantonese)-Expressive vocabulary
TOSA: The 3D Test of Spatial Assembly
